## Abstract

**Background:**

Cervical dystonia is characterized by involuntary muscle contractions of the neck and abnormal head positions that affect daily life activities and social life of patients. Patients are usually treated with botulinum toxin injections into affected neck muscles to relief pain and improve control of head postures. In addition, many patients are referred for physical therapy to improve their ability to perform activities of daily living. A recent review on allied health interventions in cervical dystonia showed a lack of randomized controlled intervention studies regarding the effectiveness of physical therapy interventions.

**Methods/design:**

The (cost-) effectiveness of a standardized physical therapy program compared to regular physical therapy, both as add-on treatment to botulinum toxin injections will be determined in a multi-centre, single blinded randomized controlled trial with 100 cervical dystonia patients. Primary outcomes are disability in daily functioning assessed with the disability subscale of the Toronto Western Spasmodic Torticollis Rating Scale. Secondary outcomes are pain, severity of dystonia, active range of motion of the head, quality of life, anxiety and depression. Data will be collected at baseline, after six months and one year by an independent blind assessor just prior to botulinum toxin injections. For the cost effectiveness, an additional economic evaluation will be performed with the costs per quality adjusted life-year as primary outcome parameter.

**Discussion:**

Our study will provide new evidence regarding the (cost-) effectiveness of a standardized, tailored physical therapy program for patients with cervical dystonia. It is widely felt that allied health interventions, including physical therapy, may offer a valuable supplement to the current therapeutic options. A positive outcome will lead to a greater use of the standardized physical therapy program. For the Dutch situation a positive outcome implies that the standardized physical therapy program forms the basis for a national treatment guideline for cervical dystonia.

**Trial registration:**

Number Dutch Trial registration (Nederlands Trial Register): NTR3437

## Background

Cervical Dystonia (CD), or torticollis, is a disabling neurological disorder characterized by abnormal positions of the head due to involuntary muscle contractions of the neck [1]. The posture in CD patients can feature one or a combination of postures: rotation (torticollis); lateral tilting (laterocollis); flexion (anterocollis); extension (retrocollis); and lateral shift. With an estimated prevalence of 5.7 patients per 100.000 persons in Western Europe, CD is the most common form of primary adult onset dystonia which usually starts after the age of 30 [2]. Pain is experienced in two-thirds to three-quarters of patients and is a major source of disability, which is strongly associated with the presence of muscle contractions and head deviations [3-6]. Decreased self-efficacy, fatigue, anxiety and depression are other factors associated with disability in cervical dystonia [7]. Research on focal dystonia’s, including CD, revealed abnormalities in basal ganglia function, cerebellar function, sensory processing, motor inhibition, neuro-plasticity and somatotopic cortical organisation but the pathophysiology remains largely unclear [8]. Treatment options for CD are mainly symptomatic, aiming to reduce involuntary movements, correct abnormal head positions and reduce pain. Currently, the best evidence based treatment option is to inject the dystonic neck muscles with botulinum toxin (BTX) [9-12]. The effects of BTX fluctuate over time. A peak effect occurs within 2–4 weeks after injections and is followed by a decrease of effect and return of symptoms. On average new injections are given within 12–14 weeks after the previous injections (Figure 1) [13].

**Figure 1 F1:**
[figure not shown]
**Effect of BTX and expected additional effect of PT.** Effect of BTX. Increasing lines indicate a better effect of BTX and less severity of CD, pain and disability to perform daily life tasks. Red lines illustrate the normal effect of BTX, blue dotted lines illustrate the expected additional effect of the PT program.

In addition to BTX treatment, many CD patients in the Netherlands are referred for physical therapy (PT). However, due to the rarity of CD, experience among Dutch PT’s is lacking. Besides, the evidence for the effects of PT on the ability to perform activities of daily living in CD is very limited. [14] Only two small Randomized Controlled Trials (RCT) and one open controlled study investigated the effects of a PT program on CD [15-17]. All studies compared BTX treatment in combination with a PT program versus BTX treatment alone. All studies showed significant better scores on pain and disability in the groups receiving BTX treatment with an additional PT program. The PT programs in all three studies consisted of intense motor learning exercises (postural control, balance, strengthening axial musculature and facilitation of voluntary movement), and mobilization techniques of the cervical spine and dystonic muscles. PT programs varied from 40 minutes per session every other day for six weeks [16], 75 minutes per session 5 days a week for five weeks [17] up to 90 minutes a day for 2 weeks [15]. Although the results of these PT treatments were positive, it is difficult to implement them to current regular care of chronic diseases provided by physiotherapists and exercise therapists. For most patients and therapists it will not be feasible to combine such an intensive program with their daily lives and practice.

One approach towards the treatment of CD was suggested by the French physiotherapist J.P. Bleton [18]. The main goals of this program are the rehabilitation of the antagonist muscles and the control of the dystonic movements by frequent training in a functional context. Exercises are taught during one or two PT sessions a week. After teaching the patients, intensive training is required in the patient’s environment (up to 10 times a day for 10 minutes). In addition, patients are encouraged to correct the dystonic posture during their daily live activities by turning their head in the opposite direction of the dystonic posture. Eventually, patients should be able to control the dystonic movements independently. This approach with increasing control of the patients and decreasing therapist involvement seems more applicable than the intensive programs by Tassoreli, El Bahwrady and Queiroz [15-17]. The effect of the Bleton treatment has never been investigated in a large randomized controlled trial. Not only for practical reasons, but also based on the pathophysiological knowledge of CD, a longer treatment period with a more functional approach and independent continuation of the treatment program seems more appropriate for the long term benefits of PT [15].

In the current study we developed a PT program with elements of the approach suggested by Bleton. We added current knowledge of motor (re) learning principles, coaching and principles of providing feedback in a standardized PT treatment program (Table 1). This resulted in a standardized, tailored PT program comprising of a one year training that aims to improve the ability to perform daily life tasks by emphasizing independent training in the patient’s own environment [18-20]. The standardized PT treatment program was developed according the AGREE standards [21] in corporation with the Royal Dutch Society for Physiotherapy (KNGF), the Society for Cesar- and Mensendieck Exercise Therapy (VvOCM) and the Amsterdam School of Health Professions (ASHP). The standardized PT program was developed within the DystonieNet, a national collaboration between neurologists and allied health professionals in research, education and treatment of CD, which was initiated by the neurology departments of four university hospitals in the Netherlands [22]. The standardized PT program aims to relearn or adopt alternative/new movement strategies to improve activities in daily life situations.

**Table 1 T1:** Theoretical background of the standardized PT program

**Muscle stretching /relaxation and mobilisations (de Morree**[43]**, Fung**[44]**)**		
*Principle*	*Explanation*	*Application in standardized PT program*
1. Passive mobilisation of the neck	Passive mobilization techniques of the neck create stress relaxation in the collagen fibers of the cervical facet joints. This helps to increase ROM	Passive mobilisation techniques are applied by PT’s
2. Muscle stretching for relaxation	Stretching elongates the dystonic muscle and helps to relax it due to the Golgi tendon reflex.	Passive stretching of dystonic muscles
**Motor learning principles (Kleim** &**Jones**[20]**)**		
*Principle*	*Explanation*	*Application in standardized PT program*
1. Use it or lose it	Failure to drive specific brain functions can lead to functional degradation.	Activation of antagonists
2. Use it and improve it	Training that drives a specific brain function can lead to an enhancement of that function.	Training of antagonists in order to improve voluntary movement of the head
3. Specificity	The nature of the training experience dictates the nature of the plasticity.	Functional training of activities of daily living tailored to the patients needs
4. Repetition matters	Induction of plasticity requires sufficient repetition.	Exercise of newly gained tasks 5–10 times a day for 10–15 minutes
5. Intensity matters	Induction of plasticity requires sufficient training intensity.	Training intensity is tailored for the individual and monitored over time
6. Time matters	Different forms of plasticity occur at different times during training.	1 year of therapy is divided in 3 stages according the 3 stages model of Fitts & Postner [45]
7. Salience matters	The training experience must be sufficiently salient to induce plasticity.	Functional training of activities of daily living tailored to the individual needs of the patient
8. Age matters	Training-induced plasticity occurs more readily in younger brains.	
9. Transference	Plasticity in response to one training experience can enhance the acquisition of similar behaviors.	Functional training of activities of daily living tailored to the patients needs and variation and random practice
10. Interference	Plasticity in response to one experience can interfere with the acquisition of other behaviors.	
**Transference and generalization (Shea** &**Morgan**[45]**, Schmidt** &**Lee**[46]**)**		
*Principle*	*Explanation*	*Application in standardized PT program*
1. Random practice	Enhances the transference and generalization of a task	Tasks or exercises are given in a random order
2. Variation of practice	Enhances the transference and generalization of a task	Specific tasks or exercises are performed in different contexts
**Feedback (Shea et al.**[47]**, Schmidt** &**Lee**[46]**)**		
*Principle*	*Explanation*	*Application in standardized PT program*
1. Summary Knowledge of Results	Feedback is essential for learning to take place. Summary KR is that KR is given after an entire set of trials during an exercise instead of after each individual trial. It is the most effective form for the retention and transference of a task.	Feedback is given after each set of trials of a task. Each task is performed at least 5 times after feedback is provided
**Self management (Fitts** &**Posner three-stage model**[48]**)**		
*Principle*	*Explanation*	*Application in standardized PT program*
1. Cognitive phase	The learner is concerned with understanding a task and developing strategies to perform a task and how the task can be evaluated. These efforts require a high degree of cognitive activity	During the first month patients receive 2 PT sessions a week to (re)learn and understand movement strategies. Movement strategies will be practiced at home 5–10 times a day for 10–15 minutes
2. Associative phase	The learner has selected the best strategy for a task and starts to refine it. This stage requires less cognitive activity	During this stage patients receive 1 PT session. Movement strategies from the first stage will be increased in difficulty. Movement strategies will be practiced at home 5–10 times day for 10–15 minutes
3. Autonomous phase	The learner is able to perform a skill automatically. A low degree of attention is required.	During the last (autonomous) stage, patients are encouraged to perform the learned tasks independently and to improve and maintain their (re)gained abilities themselves. Therapists will have a coaching role. Patients receive one PT session a month for additional advice and motivation.

The primary objective of this study is to evaluate the effectiveness of the standardized PT program on improving the ability to perform daily life activities in CD patients compared to usual PT that is given in Dutch private practices. Both PT programs are add-on treatment to BTX-injections. Measurement will take place just prior to the BTX injections as it is hypothesized that the effects of the PT program will mainly occur in the period between the injections when the BTX wears off and symptoms return (Figure 1). Secondary objectives are to evaluate the effects on severity of CD pain, quality of life, anxiety and depression.

In addition, cost effectiveness will be detremined by comparing the costs and health utility of the new standardized PT program with the care as usual PT treatment. It is hypothesized that the standardized PT program will be more cost effective and more effective in improving the ability to perform daily life tasks of CD patients than regular PT.

A positive outcome of this study will lead to the development of a national treatment guideline which will be implemented via the Dutch DystonieNet.

## Methods/design

### Study design

The study will be conducted as a multi-center single blind randomized controlled trial in three Dutch university hospitals. Patients will be randomly assigned to the experimental group or control group using a computerized randomization protocol. Patients in the expe-rimental group will be referred to specialized PT’s who are trained prior to the study to perform the standardized PT program. Patients in the control group will be referred to regular PT’s and receive care as usual. All data will be collected at baseline, after six months and after one year. In order to determine the additional effects of a PT program, measurements will be performed briefly before the BTX injections at the outpatient clinics of the hospitals. This implies that we measure the effect of the PT program in a period that BTX has the least effect on the symptoms of dystonia (Figure 1). Measurements will be performed by a blind and independent assessor since it is impossible to blind the therapists and patients for treatment allocation.

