#### Regular PT

Subjects randomized in this group will receive BTX injections and regular PT once a week for a period of one year. In contrast to the standardized PT program, interventions are not given by specialized therapists. Due to the rarity of CD, the average therapist in the Netherlands has little knowledge about CD. It is likely that common interventions like massage, stretching and exercise of the dystonic muscles are used. Specific information of the weekly sessions and treatment will be retrieved from the local PT’s after the patients finished the study period of one year.

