### Sample size

The power calculation is based on the study by Brans et al. investigating the long term effect of BTX on disability and functional health [41]. This study showed an average improvement of 7.1 out of 30 points on the disability subscale of the TWSTRS after 1 year of BTX treatment in CD patients. It is estimated that the additional effect of the PT program according the treatment guideline will be at least half the effect caused by BTX. The cut off for the success of the PT program is therefore, set on an average improvement of 3.5 out of 30 points on the TWSTRS disability scale which is clinically relevant according Brans et al. [42]. With a power of 0.80 and an alpha of 0.05, each group will need 44 subjects. With a loss of 10% taken into account, 50 subjects in each group are required.

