### Analysis

Differences in all outcome measures, with exception of the measures for cost effectiveness, will be determined with a mixed between-within (repeated measures) analysis of variance for both treatment arms, across three time periods (baseline, after six months and one year). All analyses will be performed under the intention to treat principle in SPSS 20.0. Differences will be considered significant at p-value < 0.05.

The cost effectiveness will be determined by a cost-utility analysis from a societal perspective with a time horizon of one year. Cost-utility analysis facilitates the comparative assessment of health care innovations across different types of interventions, disease areas and health care settings. Incremental cost-utility and cost-effectiveness ratios for the add-on standardized PT program versus add-on regular PT will be calculated as the extra costs per QALY gained and the extra costs per unit decrease in TWSTRS-disability score. The cost effectiveness will be calculated according the most recent guidelines for unit costing in healthcare research [40]. The friction cost method will be applied to calculate the costs of production loss as measured with the PCQ, EQ-5D. Unit costs of production loss will be based on the most recent national guidelines for unit costing in healthcare research [40]. The base year for unit costing will be 2013.

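### The analysis and sample size make no allowance for patients who share a therapist, so the standard error of the programme effect may be too small

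*Protocol article*

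**What the plan says.** Under Study design, the protocol article randomises individual patients to two arms. Those in the experimental arm are referred to specialised physical therapists "who are trained prior to the study to perform the standardized PT program". Under Regular PT, the control arm differs in that "interventions are not given by specialized therapists"; its therapists are described as local ones with little knowledge of the disease. The number of therapists and the number of trial patients per therapist are not given for either arm.

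Under Analysis, the clinical outcomes are to be compared with a "mixed between-within (repeated measures) analysis of variance for both treatment arms" over three time points. No therapist term is named.

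Under Sample size, the target difference is "set on an average improvement of 3.5 out of 30 points on the TWSTRS disability scale", and the result reads "With a power of 0.80 and an alpha of 0.05, each group will need 44 subjects". The only inflation is for drop-out: "With a loss of 10% taken into account, 50 subjects in each group are required". No standard deviation, ICC or design effect is stated.

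**The concern.** When one therapist treats several patients, their outcomes tend to be alike because they share that therapist's skill and style. The experimental programme leaves room for this. Table 1 describes passive mobilisation and stretching by the therapist, individually tailored training intensity, structured feedback, and a coaching role in the last stage. Therapist effects arise after randomisation, so comparing change from baseline does not remove them.

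The two arms also draw on different pools. Experimental therapists must be trained in advance, whereas controls attend ordinary local practices. Given the rarity of the disease, sharing is probably more common in the experimental arm. The design is then partially nested, and a two-arm ANOVA that treats patients as independent does not represent it.

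Two things are at stake. The p-value and confidence interval for the programme effect could be too optimistic. In addition, the article intends a positive result to be the basis of a national guideline, to be used by therapists outside the trial. That inference needs variation between therapists in the standard error.

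**Working it through.** **Inputs from the protocol article (Sample size):** difference 3.5 points, power 0.80, alpha 0.05 (taken as two-sided; the article does not say), 44 evaluable per group, 10% loss.

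**Inputs assumed:** m = 2 to 10 trial patients per trained therapist; therapist ICC = 0.01 to 0.10; clustering in the experimental arm only; equal caseloads; the same total SD in both arms.

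**Step 1: the plan's own figure.** No SD is given, so 44 cannot be derived from the stated inputs. Solving backwards:

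SD = 3.5 × √(44/2) / (1.960 + 0.842) = 16.42 / 2.802 ≈ 5.86.

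A t-based solution gives 5.79, and a one-sided test would imply 6.60. The figure of 44 is therefore plausible for simple independent groups and shows no visible room for a design effect. For drop-out, 44/0.9 = 48.9, or 49; the stated 50 leaves 50 × 0.9 = 45 evaluable.

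**Step 2: effect of clustering in one arm.**

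- Design effect in the experimental arm: DE = 1 + (m − 1) × ICC.
- Ratio of the true to the naive standard error: f = √((DE + 1)/2).
- Type I error if the naive analysis is kept: 2 × (1 − Φ(1.960/f)).
- Power of a test that uses the correct standard error: Φ(2.802/f − 1.960).
- Evaluable patients per arm for 80% power: (DE + 1) × 22, rounded up, since 44 = 2 × 22.

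| m | ICC | DE | f | Type I error | Power | n per arm |
|---|---|---|---|---|---|---|
| 1 | any | 1.00 | 1.000 | 5.0% | 80.0% | 44 |
| 2 | 0.01 | 1.01 | 1.002 | 5.1% | 79.8% | 45 |
| 2 | 0.05 | 1.05 | 1.012 | 5.3% | 79.0% | 46 |
| 5 | 0.01 | 1.04 | 1.010 | 5.2% | 79.2% | 45 |
| 5 | 0.05 | 1.20 | 1.049 | 6.2% | 76.2% | 49 |
| 5 | 0.10 | 1.40 | 1.095 | 7.4% | 72.5% | 53 |
| 10 | 0.05 | 1.45 | 1.107 | 7.7% | 71.6% | 54 |
| 10 | 0.10 | 1.90 | 1.204 | 10.4% | 64.3% | 64 |

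Worked example, m = 10 and ICC = 0.10: DE = 1 + 9 × 0.10 = 1.90; f = √(2.90/2) = 1.204; 1.960/1.204 = 1.628, so type I error is 10.4%; 2.802/1.204 − 1.960 = 0.367, so power is 64.3%.

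**Step 3: limits of the calculation.** Type I error and power in one row describe different analyses: the first is the price of keeping the naive test, the second that of correcting it. The formulas are a normal approximation for two means, not the arm-by-time ANOVA itself. With few therapists the correct test also loses degrees of freedom: at m = 10, 44 patients mean 44/10 = 4.4, so four or five therapists, and power would be below the tabulated value. If controls share therapists to the same degree, power falls further, for example to 72.5% instead of 76.2% at m = 5 and ICC 0.05.

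**The case against.** The strongest objection is that the premises about caseload are not in the document. A reader might infer that a small set of trained therapists treats several trial patients each while every control has a therapist of his or her own, and that the standard errors are therefore too small. The article supports none of this outright. Patients come from three hospitals and the programme starts with two sessions a week, so there could equally be many trained therapists close to patients' homes with one or two patients each. At m = 2 and ICC 0.05 the effect is negligible. This part of the objection stands, and the point is conditional.

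The ICC may also be low. The programme is standardised, much of it is practised at home, and contact falls to one session a month in the last stage. That is a fair reason to start the range at 0.01. Blinded assessment helps less, because it protects measurement and does not remove real differences between therapists.

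A reader might also say that the plan treats all outcomes as independent. That goes too far: the ANOVA models repeated measures within a patient. Only independence between patients of the same therapist is assumed.

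Finally, this is a condensed article, and a full protocol or SAP may hold more detail. Therapist numbers could well be there, and their absence here is not the point. But the article names a specific model and justifies a specific sample size, and neither accommodates shared therapists. A SAP could change the model; it would not change the basis on which 44 per group was set.

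**Conclusion.** The point holds in conditional form. The stated ANOVA and the 44 per group treat patients who share a therapist as independent, in a design where sharing is likely and probably uneven between arms. If trained therapists treat more than one trial patient and the ICC is above 0, the standard error of the programme effect is too small by a factor of 1.002 to 1.204 over the assumed range. The consequence runs from negligible to material. It rests on assumed values of m and ICC, a back-solved SD of about 5.86, and clustering in the experimental arm only. The documents do not allow a firm statement that the standard errors are wrong, or by how much. The change is worth making because it costs little and does no harm if clustering proves absent.

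**What to change.** 1. Record the treating therapist for every patient in both arms. For controls, contact with the local therapists is already planned under Regular PT.
2. Analyse the primary outcome with a partially nested mixed model: a therapist random effect in the experimental arm, and in the control arm too if therapists are shared there; arm-specific residual variance; and a small-sample correction to the degrees of freedom. Keep the within-patient correlation over the three time points.
3. State the number of trained therapists and restate power over a range of design effects based on it, without enrolling more patients.

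The cost is one extra variable, one model term and a lower stated power. The confidence interval could be up to about 20% wider at the upper end of the range from the standard error alone (f = 1.204), and somewhat more after the degrees-of-freedom correction if therapists are few. At about two patients per therapist the change would hardly be visible.
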